### Statistical methods

To evaluate the effectiveness of CIS as compared to SOC on the combined outcome of linkage to HIV care within 1 month and retention in care at 12 months among adults testing HIV positive.An intent-to-treat analysis will be used to compare the combined outcome of linkage to HIV care within 1 month and retention at 12 months between participants at sites randomized to receive the SOC and participants at sites randomized to receive CIS. We will use multilevel generalized linear regression models to provide statistical estimates controlling for cluster and matched stratum effects. Models will include fixed effects for study condition (treatment arm) and random effects for sites. This approach will take into account the correlation among participants within facilities. In addition, we will compare patient-level and facility-level characteristics hypothesized to influence linkage and retention after data collection has been completed in order to assess whether the randomization evenly distributed important non-matched predictors of linkage and retention between intervention and control arms. Covariates hypothesized to influence linkage and retention that will be analyzed include: actual numbers of adults enrolling in HIV care at each site during the study period, age, gender, baseline measures of CD4 count and WHO stage at enrollment into HIV care, and tuberculosis status at enrollment into HIV care. Should important differences be observed between intervention and control arms, we will additionally conduct covariate-adjusted generalized linear mixed models to assess the degree to which these differences alter our measures of association.To evaluate the incremental effectiveness of CIS + FI compared to CIS on the combined outcome of rapid linkage to HIV care within 1 month and retention in care at 12 months among adults newly diagnosed with HIV.The approach for this objective will follow the approach outlined under objective 1 above; in this case, the combined outcome will be compared between participants enrolling in cohort 3 (receiving CIS + FI) and those enrolling approximately six months earlier in cohort 2 (receiving CIS without FI), all within the same study arm.To evaluate the effectiveness of CIS compared to SOC and the incremental effectiveness of CIS + FI compared to CIS in relation to: linkage to care within one month; retention 12 months after HIV diagnosis; time from eligibility to ART-initiation, and disease progression.Outcomes will be compared under an “intent to treat” scenario and, if significant differences in other determinants of these outcomes are observed between study cohorts at baseline, generalized multilevel mixed models will be used to compare outcomes between study cohorts. In addition, linkage rates and non-retention and mortality rates 12 months after HIV diagnosis will be compared between study arms using Kaplan-Meier survival analytic techniques using robust sandwich estimates to account for clustering. Participants who are lost to follow-up will be censored for mortality and morbidity analyses at the time of last known visit. For the subset of participants determined ART eligible at their site, Cox Proportional Hazards Models will be used to compare the time from ART eligibility to ART initiation between participants receiving CIS + FI, CIS and SOC, censoring participants transferring after ART eligibility but before initiation and treating participants who die before ART initiation as competing risks, and using robust sandwich estimates to account for clustering.To evaluate the cost-effectiveness of CIS compared to SOC and the incremental cost-effectiveness of CIS + FI compared to CIS.The incremental cost-effectiveness ratio is defined as the incremental change in costs divided by the incremental change in effects. This study will use cost-effectiveness to compare SOC with CIS, CIS with CIS + FI, and SOC with CIS + FI. The incremental cost-effectiveness of CIS compared to SOC is equal to the cost of CIS minus the cost of SOC divided by the effectiveness of CIS minus the effectiveness of SOC. In discounting future benefits expected from long-term benefits of the proposed intervention (such as improved life expectancy), we will explore alternative time horizons (ranging from the period of data collection to five years, 10 years, 20 years, and lifetime), and we will use the standard discount rate of 3% for costs and benefits. This discount rate reflects the time preference with regard to costs and benefits (that is, a dollar today is worth more than an inflation-adjusted dollar at some time in the future). The downstream impact of CIS and CIS + FI on future costs and benefits (e.g. the potential impact of prolonging lives) will be included as additional costs and benefits.To assess feasibility and participant acceptability of the interventions included in CIS and CIS + FI in enhancing linkage and retention.To assess feasibility of CIS and CIS + FI, uptake of interventions will be assessed by calculating the proportion of participants reporting that they received each intervention during the 1- and 12-month follow-up interviews and documented within study records as having received them. To assess acceptability, participants are asked to identify whether each intervention was helpful in terms of assisting in timely linkage to care and retention after enrollment into care, the “most useful” and “least useful” intervention, and to identify what aspects of each intervention were useful and not useful. Stratified analyses will examine associations between participant socio-demographic and clinical characteristics and acceptability.

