**Table 2 Tab2:** **Combination intervention strategy interventions compared to standard of care**

Intervention	Standard of care	CIS (CIS, CIS + FI)	Barriers targeted by interventions
**CD4 testing**	CD4 (Cyflow, FACS Caliber/Count, POC CD4) at HIV care site laboratory if linkage completed.	POC CD4 assays at HIV testing points.	Structural
	Turnaround time: 1–4 weeks.	Turnaround time: immediate.	
**Accelerated ART initiation**	Within 1–2 months from linkage.	Accelerated ART initiation within 1 week from testing.	Biomedical
	2-3 counseling sessions, all in HIV care.	2 counseling sessions, one in HCT immediately following POC CD4 test and one in HIV care.	
	Baseline laboratory tests results obtained prior to initiation.	Draw blood for baseline laboratory tests, and initiate prior to results.	
**Cellular appointment reminders**	None.	SMS appointment reminders for all participants.	Behavioral
**Non-cash financial incentives**	None.	Pre-paid cellular air time cards.	Structural

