#### Combination Intervention Strategy (CIS)

In order to most closely approximate “real-life” service delivery, the clinical interventions of the CIS package (i.e. POC CD4 count testing and accelerated ART initiation) are provided by clinic staff to all patients receiving care at the facility, not solely study participants. Study personnel provide SMS appointment reminders and, for participants in the CIS + FI cohort, FI only to study participants. Each of these interventions is described below.

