#### POC CD4 count testing

Patients at the intervention sites receive a POC CD4 count test in the HCT point of service immediately following HIV diagnosis by the HCT counselor. Results are available and provided to the patient along with an explanation of their meaning within 20 minutes. All patients, regardless of CD4 count, are provided with a referral slip for the on-site HIV care clinic and instructed to enroll in care as soon as possible, although particular emphasis on prompt enrollment is provided to patients who are ART eligible as described below. Patients not yet eligible for ART who agree to enroll in HIV care immediately are escorted to the receptionist’s office, whereas those who are ART eligible receive the accelerated ART initiation intervention described below.

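### The balance check and the additional adjusted model use covariates that depend on linkage or may be changed by the intervention, so both can mislead; the primary unadjusted estimate is not affected

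*Protocol article*

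**What the plan says.** Under Statistical methods, the Protocol article makes the primary comparison of CIS with SOC an intent-to-treat multilevel model: "Models will include fixed effects for study condition (treatment arm) and random effects for sites", with control for matched stratum and no patient covariates.

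After data collection, patient and facility characteristics are to be compared between arms to see whether randomization balanced them. The list is age, gender, "actual numbers of adults enrolling in HIV care at each site during the study period", and "baseline measures of CD4 count and WHO stage at enrollment into HIV care, and tuberculosis status at enrollment into HIV care". The consequence of imbalance is then stated: "Should important differences be observed between intervention and control arms, we will additionally conduct covariate-adjusted generalized linear mixed models". The purpose is to see how far such differences alter the estimated association.

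Elsewhere the article shows when these variables arise:

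- **SOC arm, CD4 (Table 2):** "CD4 (Cyflow, FACS Caliber/Count, POC CD4) at HIV care site laboratory if linkage completed". The Standard of Care section agrees: blood is drawn after the first consultation in HIV care.
- **Intervention sites, CD4 (POC CD4 count testing):** "Patients at the intervention sites receive a POC CD4 count test in the HCT point of service immediately following HIV diagnosis".
- **WHO stage and tuberculosis status:** timed at enrollment into care in both arms. Neither is among the baseline questionnaire contents listed under Participant interviews, and clinical data come from existing electronic databases.
- **Reach of the intervention (Combination Intervention Strategy):** "the clinical interventions of the CIS package (i.e. POC CD4 count testing and accelerated ART initiation) are provided by clinic staff to all patients" at the facility, not only to study participants.

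**The concern.** A balance check on randomization, and any adjustment that follows from it, needs variables that the intervention cannot affect and that are known for everyone. Enrollment into care is the event that CIS is meant to bring about, and it is half of the primary endpoint. Variables that come into existence at that event are known only for people selected by the outcome.

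CD4 count has a further problem, because the selection works in one arm only. The check would compare SOC participants who linked with all CIS participants. If the CIS value were instead taken at enrollment into care, as the list literally reads, it would compare linkers with linkers, where linking itself depends on treatment. Either way a difference says nothing about the randomization, yet it would trigger the adjusted model.

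Enrolment volume during the study is a different case. It is not missing for anyone, but because the clinical components reach all patients at a CIS site, it may be a consequence of allocation. Adjusting for it could remove part of the effect.

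The adjusted model will be read as a test of whether the main result survives imbalance. If it is biased, it could appear to contradict a sound primary estimate, or to reinforce it falsely. The CIS + FI comparison is to follow the same approach, and its incentives reward linkage, so WHO stage and tuberculosis status carry the same difficulty there.

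**Working it through.** **Inputs**

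- SOC: 50% link within 1 month and 50% of these are retained (Sample size and power analysis).
- CIS combined outcome: 45% (same section).
- 750 participants per cohort (Study sites and participants).
- Share linking within three months in sub-Saharan Africa, judged by receipt of a CD4 count: 59% to 78% (Background).
- Assumption, not in the article: participants with a missing covariate are dropped (complete case).
- Assumption: every participant who meets the combined outcome has the covariates.

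**Plan's own figure.** SOC success = 0.50 × 0.50 = 0.25, as stated. With everyone kept, the contrast is 0.45 − 0.25 = +20 points, odds ratio (0.45/0.55)/(0.25/0.75) = 2.45.

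**Who could be dropped in SOC.** Of 750, 375 do not link by 1 month, 187.5 link but are not retained, and 187.5 succeed. Failures number 562.5, so those not linked by 1 month are 375/562.5 = two thirds of them.

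**CD4 only.** Let S be the share of SOC participants with a CD4 count. CIS stays at 0.45, because CD4 is measured at the test. The complete-case SOC rate is 0.25/S.

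| S | SOC rate | CIS − SOC |
|---|---|---|
| 0.50 | 0.500 | −5 points (odds ratio 0.82) |
| 0.556 | 0.450 | 0 |
| 0.59 | 0.424 | +3 |
| 0.70 | 0.357 | +9 |
| 0.78 | 0.321 | +13 |

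The sign changes only if S < 0.25/0.45 = 0.556. The row S = 0.50 requires that nobody in SOC links after month 1.

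**WHO stage or tuberculosis status in the model.** CIS participants who never enter care are now dropped too. Let L be the CIS share that ever enters care. The contrast is 0.45/L − 0.25/S.

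| S | L = 0.60 | L = 0.70 | L = 0.80 | L = 0.90 | L = 1.00 |
|---|---|---|---|---|---|
| 0.50 | +25 | +14 | +6 | 0 | −5 |
| 0.60 | +33 | +23 | +15 | +8 | +3 |
| 0.70 | +39 | +29 | +21 | +14 | +9 |

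Reversal needs L/S > 0.45/0.25 = 1.8. Several cells exceed the true +20 points, so the bias can also inflate the effect.

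**Sensitivity to the CIS rate.** The sample size section also gives a relative risk of 1.6, which implies 0.25 × 1.6 = 40%, not 45%. The true contrast would then be +15 points, and CD4-only adjustment would give 0.40 − 0.25/0.59 = −2 to 0.40 − 0.25/0.78 = +8 points, with the sign changing below S = 0.25/0.40 = 0.625. The main tables use 45% because the article states that figure for the CIS arm.

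**Enrolment volume.** The article gives no figure from which a size could be computed; the argument rests on the reach of CIS alone.

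**The case against.** The strongest reply is that the primary analysis contains none of these covariates. The adjusted model is conditional and extra: "we will additionally conduct covariate-adjusted generalized linear mixed models to assess the degree to which these differences alter our measures of association". A reader might infer that the primary result itself could be reversed. The document does not support that; the model could only produce a conflicting secondary estimate. This part of the reply stands in full.

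Second, the article does not say how missing covariates are handled, and may leave that to the analysis plan. This also stands: the figures above are an illustration. It does not rescue the choice of covariates. No SOC participant who never links has a CD4 count under the described procedures, so imputation would extrapolate entirely from linkers. A missing-value indicator would flag people who have already failed the endpoint. Nor does missing-data handling repair the balance check or the volume covariate.

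Third, −5 points is an extreme case. Linkage within 12 months is a secondary objective, so later linkage is expected, and the Background range of 59% to 78% lies above the 55.6% threshold. That range is regional and refers to three months, so it is only a guide, but at the 45% planning rate it points to attenuation rather than reversal.

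Fourth, it would be wrong to say that the covariates exist only for linkers, or that adjustment deletes the SOC failures. CD4 exists for all tested patients at intervention sites, and at most about two thirds of SOC failures would be lost.

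**Conclusion.** The point holds for the balance check and for the additional adjusted model. Three listed covariates depend on linkage, in SOC only for CD4 as measured and in both arms for WHO stage and tuberculosis status. The fourth may be changed by the intervention. The check cannot speak to randomization and can itself generate the differences that start the adjustment.

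The bias has no predictable direction. With complete-case handling, planning rates of 25% and 45% and 59% to 78% of SOC participants having a CD4 count, adjusting for CD4 alone would reduce +20 points to about +3 to +13. With WHO stage or tuberculosis status included, the result depends on linkage in each arm and may fall below, above or on the other side of zero from the true value. It would be too strong to conclude that adjustment always pulls towards no effect, or that the trial's main finding is at risk.

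Severity: should be fixed. The list is a stated choice, not a detail left to another document, and the unadjusted intent-to-treat estimate stands regardless.

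**What to change.** Remove CD4 count, WHO stage, tuberculosis status and actual study-period enrolment volume from both the balance check and the adjustment set. Report the three clinical variables descriptively among participants who link, labelled as such.

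Pre-specify the adjusted model and run it whatever imbalance is seen. Use variables held on every participant at the HIV test: age, gender, and the baseline questionnaire's socio-demographic, travel and testing-history items. Add the pre-study expected enrolment volume used for matching, as a number if it is held. The two classes shown in Table 1 are identical within every matched pair and would add nothing once matched stratum is controlled.

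Do not add testing point. In Table 1, PICT occurs at two SOC sites and at no CIS site, so that adjustment would rest on extrapolation.

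Apply the same set to the CIS + FI comparison and to the secondary outcomes.

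The cost is a change of wording; the replacement variables are already collected or were used for matching. The downside is that the adjusted model no longer accounts for disease stage.

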### Sample size and power analysis

Based on a review of the relevant literature, under the current SOC in Mozambique we conservatively estimated that the combined outcome of linkage within 1 month and retention at 12 months after HIV diagnosis would be 25% (assuming 50% of participants enroll into HIV care within 1 month of diagnosis and 50% of these are retained in care 12 months after diagnosis). We then estimated the minimum difference we could detect in our combined outcome between CIS and SOC arms with 80% power using the Power and Sample Size (Pass 8.0) software for two independent proportions in a cluster randomization study design and a two-sided Farrington & Manning Likelihood Score Test [34], and assuming five study clusters (two sites per cluster) and 300 patients per cluster. With these assumptions, we will have 80% power to detect as statistically significant a relative risk of the combined outcome of linkage and retention between CIS and SOC arms of 1.6 (or an absolute increase in the combined outcome of 20%) comparing the CIS to SOC arms.

To address the objective of comparing the effectiveness of CIS + FI to CIS on the combined outcome of linkage within 1 month of diagnosis and 12 month retention after diagnosis, we are enrolling an additional 150 participants in each of the five CIS sites (total of 750 additional participants in intervention arm) in cohort 3 (CIS + FI) upon completion of enrollment of cohort 2 (CIS). Assuming that the combined outcome of linkage within one month of diagnosis and retention 12 months after diagnosis is 45% in the CIS arm, we will also have greater than 80% power to detect an absolute increase of 21% in the combined outcome comparing CIS + FI to CIS.

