### Trial status

The study was launched in April 2013 at two sites in Maputo and all sites were actively enrolling participants for the SOC arm and CIS cohort of the intervention arm by December 2013. The first round of the site assessment was conducted in April 2014. As of July 2014, enrollment is complete at eight sites (four SOC sites and four intervention sites) with a total of 1351 participants enrolled. Enrollment of CIS + FI participants began at two intervention sites in June 2014.

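### The CIS + FI versus CIS comparison inherits a site-random-effect model that allows no site-by-period variation, so its standard error is too small if sites shift differently between cohorts

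*Protocol article*

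**What the plan says.** All references are to the protocol article. Under Statistical methods, the CIS versus SOC comparison uses multilevel generalized linear models "controlling for cluster and matched stratum effects", and the terms are named: "Models will include fixed effects for study condition (treatment arm) and random effects for sites". For CIS + FI versus CIS the text adds only that "The approach for this objective will follow the approach outlined under objective 1 above". The comparison is between cohort 3 and "those enrolling approximately six months earlier in cohort 2 (receiving CIS without FI), all within the same study arm".

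Covariate adjustment is conditional on important imbalance. The candidates are "actual numbers of adults enrolling in HIV care at each site during the study period, age, gender, baseline measures of CD4 count and WHO stage", together with tuberculosis status. Neither enrolment date nor period is among them.

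Study design describes the incentive comparison as a pre-post design nested in the intervention arm. Cohort 3 follows completion of cohort 2, and the SOC cohort is enrolled alongside cohort 2. Sample size and power analysis gives 150 further participants at each of the five CIS sites, a 45% success rate under CIS, and "greater than 80% power to detect an absolute increase of 21% in the combined outcome comparing CIS + FI to CIS".

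**The concern.** The two comparisons have different error structures. CIS versus SOC compares different sites, so variation between sites is the relevant noise, and a site random effect captures it. CIS + FI versus CIS compares each site with itself at a later time. The stable part of a site's level cancels, and the relevant noise between clusters is how far each site's own level moves from one period to the next. A site intercept gives that movement no variance. The matched-stratum term does not help: Table 1 shows one CIS site in each pair, so within the intervention arm stratum and site coincide.

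A second, separate problem is bias. Within a site, cohort and period coincide, so a change common to all sites is estimated as incentive effect.

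This comparison is half of the primary objective, and its effect estimate is the denominator of the CIS + FI versus CIS cost-effectiveness ratio. A false positive would be read as evidence for paying incentives.

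**Working it through.** **Inputs from the article.** Five sites, 150 per site per cohort (750 per cohort), success rate p = 0.45 under CIS, so pq = 0.45 × 0.55 = 0.2475.

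**Assumptions.** Two-sided alpha 0.05, ICC 0.02 to 0.05, and a correlation r between a site's underlying rates in the two periods. The article states none of these.

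**1. The plan's own figure.** With effective n = 750/(1 + 149 × ICC) per cohort and a pooled two-proportion test, 80% power for 25% versus 45% implies ICC 0.050. The same ICC gives 81% power for 45% versus 66%. Solving instead from the stated relative risk of 1.6 (25% versus 40%) gives ICC 0.026 and 96% power for 45% versus 66%. Both agree with a claim of more than 80%. The figure cannot be reproduced uniquely because no ICC is given.

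**2. Variance of the estimated difference.**
- Variance under a site-intercept model: 2pq(1 − ICC)/750.
- Variance added by site-by-period movement: 2pq × ICC × (1 − r)/5.
- Ratio of true to model variance: 1 + 150 × ICC × (1 − r)/(1 − ICC).

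Example, ICC 0.05 and r = 0.8:
- Model variance: 2 × 0.2475 × 0.95/750 = 0.000627, SE 2.5 points.
- Added variance: 2 × 0.2475 × 0.05 × 0.2/5 = 0.000990.
- True variance: 0.001617, SE 4.0 points. Ratio 2.58; SE ratio 1.61.
- Type I error: P(|Z| > 1.96/1.606) = P(|Z| > 1.22) = 22%.

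**3. Type I error over the assumed range (no incentive effect, no trend).**

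| r | ICC 0.02 | ICC 0.05 |
|---|---|---|
| 1.0 | 5% | 5% |
| 0.95 | 7% | 10% |
| 0.9 | 9% | 14% |
| 0.8 | 12% | 22% |
| 0.7 | 16% | 29% |

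Simulation of a site-stratified test, standing in for the site-intercept model, agrees within about one percentage point (22% at ICC 0.05, r = 0.8). With site effects simulated on the logit scale, that cell is 18-19%. A linear mixed model with only a site intercept, at ICC 0.045 and r = 0.8, gave 18% in 300 runs.

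**4. The alternative test.** A paired t-test on the five site-level changes (4 degrees of freedom) stays at about 5% in every cell. Its simulated power for +21 points is at least 99% at ICC 0.02; at ICC 0.05 it is 99% at r = 0.9, 97% at r = 0.8 and 92% at r = 0.7.

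**5. Width of the interval.** At ICC 0.05 and r = 0.8, the site-intercept 95% interval is about ±1.96 × 2.5 = ±4.9 points. The 4-df interval is about ±2.776 × 4.0 = ±11.2 points.

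**6. Trend.** A common rise between cohorts is added in full to the estimate. With 750 per cohort and no site-by-period variation, a rise of 2, 3, 5 or 10 points alone gives a significant result with probability 12%, 21%, 49% or 97%. Allowing for site-by-period variation does not remove this: with a 5-point trend the mean paired difference in simulation is still about 5 points.

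**The case against.** The strongest reply has three parts.

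*The article is condensed.* Random-effect structure and degrees of freedom are often left to the full protocol or SAP, and random effects for sites need not exclude a cohort effect that varies by site. This has some force, but the article does name the model terms and transfers them to a different design with no change. If a fuller document has the extra term, only the wording here needs correcting.

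*The size depends on unstated quantities.* This stands. At between-period correlation 1 there is no inflation, and at 0.95 it is modest.

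*Trend is inherent in a design openly called pre-post.* This also stands. It is a limit of the design and not a modelling slip; disclosure does not remove it from the estimate, but no model term fully cures it.

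Three stronger readings are tempting and are not supported:

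- A reader might infer that the 21-point power figure is wrong because it resembles a calculation for independent sites. It is stated as more than 80%, no ICC is given, and the within-site test exceeds 80% in every case examined. At most it is conservative.
- A reader might set the six-month gap against Trial status: "The study was launched in April 2013 at two sites in Maputo", while "Enrollment of CIS + FI participants began at two intervention sites in June 2014". That is 14 months between two study-level dates. The article does not say which sites launched first or which began incentives. All sites were enrolling by December 2013, six months before June 2014. No cohort-level gap can be computed, so no contradiction is shown.
- A reader might take the strike, absences and shortages in the Discussion as proof of site-specific changes in outcome. The text says that they delayed recruitment. They make changing conditions plausible but do not show that sites diverged between cohorts.

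**Conclusion.** The concern holds in a conditional form. The model stated for CIS + FI versus CIS leaves out the variance component that governs a same-site, successive-cohort comparison. If sites move differently between periods, type I error exceeds 5%: about 9-29% for ICC 0.02 to 0.05 with correlation 0.9 to 0.7, and about 7-10% at 0.95. It is 5% only if the correlation is exactly 1. Both parameters are assumptions, and so is alpha 0.05.

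The trend bias is a separate matter. It equals whatever common change occurs between cohorts, its size is unknown, and it follows from the design. It bears on how the result is labelled and tested for sensitivity.

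Neither part shows the stated power or the stated gap between cohorts to be in error.

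**What to change.** 1. For the CIS + FI versus CIS objective, replace the reference back to objective 1 with its own model: add a site-by-cohort random effect and test the cohort effect on 4 degrees of freedom, or use a paired t-test on the five site-level changes.
2. Report the contrast as a non-randomised pre-post comparison, distinct from the randomised CIS versus SOC result.
3. Add a trend sensitivity analysis under a stated parallel-trend assumption, using enrolment month or the same-period change in retention after enrolment at the SOC sites from the clinic database. State its limits: cohort and period coincide within a site, so enrolment month separates them only in part, and the database covers patients enrolled in care, so it can inform retention but not linkage or the composite.

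The 21-point figure and the six-month description need no change on this account.

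The cost is revised analysis wording and a modest amount of analysis, with no new participants. Confidence intervals widen, for example from about ±5 to about ±11 points at ICC 0.05 and correlation 0.8, while power for 21 points stays above 80% under the assumptions shown.

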### Secondary objectives

The secondary objectives include to: 1) evaluate the effectiveness of CIS compared to SOC and the incremental effectiveness of CIS + FI compared to CIS in distinct steps along the HIV care continuum, including linkage to HIV care within 12 months from positive HIV test, retention in care at 12 months from positive HIV test, time from ART eligibility to ART initiation, and disease progression (new World Health Organization [WHO] stage III/IV event, hospitalization, CD4 count, death); 2) evaluate the cost-effectiveness of CIS compared to SOC and the incremental cost-effectiveness of CIS + FI compared to CIS; and 3) assess feasibility and participant acceptability of the relative benefit of the interventions included in CIS and CIS + FI in enhancing linkage and retention.

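### Kaplan-Meier is planned for linkage to 12 months although death rules linkage out; with deaths censored, cumulative linkage is slightly overstated, while the same section makes death a competing risk for ART initiation

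*Protocol article*

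**What the plan says.** The Statistical methods section of the protocol article, under the secondary effectiveness outcomes, plans that "linkage rates and non-retention and mortality rates 12 months after HIV diagnosis will be compared between study arms using Kaplan-Meier survival analytic techniques", with sandwich estimates for clustering. The sentence after it gives a censoring rule: "Participants who are lost to follow-up will be censored for mortality and morbidity analyses at the time of last known visit". That rule concerns loss to follow-up, and only in mortality and morbidity analyses. Neither sentence says what happens in the linkage and non-retention curves when a participant dies.

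For time from ART eligibility to ART initiation the section is explicit. It plans Cox models, "censoring participants transferring after ART eligibility but before initiation" and "treating participants who die before ART initiation as competing risks".

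The Secondary objectives section includes "linkage to HIV care within 12 months from positive HIV test", and lists death as one component of disease progression. No expected mortality is given anywhere in the article.

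**The concern.** Death before linkage makes linkage impossible. Kaplan-Meier with deaths censored treats the dead as if they could still link at the same rate as those alive and unlinked. The curve then estimates linkage in a hypothetical population without deaths, not the proportion of enrolled adults who link. The direction of the error is fixed: the estimate is too high whenever anyone dies unlinked.

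The article recognises this structure one step later in the care continuum, at ART initiation, and linkage has the same structure. So this is more than a detail left out of a condensed article: a method is named for linkage that does not fit the way death is handled for a parallel outcome.

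At stake are the 12-month linkage proportions reported for a stated secondary objective and, if deaths before linkage differ between arms, a small part of the difference between them.

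**Working it through.** The plan states no figure for these curves, so there is none to reproduce. The check compares one minus Kaplan-Meier (deaths censored) with the cumulative incidence of linkage (death as a competing event) under stated assumptions.

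**Inputs from the article**
- Linkage under standard of care: "assuming 50% of participants enroll into HIV care within 1 month of diagnosis" (Sample size and power analysis).
- Retention: "50% of these are retained in care 12 months after diagnosis" (same section), so non-retention among the linked is 50%.
- The Background section cites 59-78% linked within three months. It guided the choice of 12-month linkage below.

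**Assumptions, not in the article**
- 12-month mortality m of 2% to 20%, with a constant death hazard independent of linkage: d = -ln(1 - m)/12 per month.
- Linkage net of death of 60%, 70% or 78% at 12 months.

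**Linkage formula.** Let L be 12-month linkage net of death. The monthly linkage hazard is h1 = -ln(0.5) = 0.6931 in month 1, then h2 = -ln((1 - L)/0.5)/11.
- One minus Kaplan-Meier = L.
- Cumulative incidence = h1/(h1 + d) × [1 - exp(-(h1 + d))] + exp(-(h1 + d)) × h2/(h2 + d) × [1 - exp(-11(h2 + d))].

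**Worked case, L = 60%, m = 5%.** d = 0.00427 and h2 = 0.02029. The first term is 0.9939 × 0.5021 = 0.4991. The second is 0.4979 × 0.8260 × 0.2367 = 0.0974. The sum is 59.6%, against 60.0% from Kaplan-Meier, an overstatement of 0.4 points.

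Cumulative incidence of linkage at 12 months:

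| Assumed mortality | KM 60% | KM 70% | KM 78% | Overstatement (points) |
|---|---|---|---|---|
| 2% | 59.9% | 69.8% | 77.7% | 0.1-0.3 |
| 5% | 59.6% | 69.4% | 77.2% | 0.4-0.8 |
| 10% | 59.3% | 68.8% | 76.4% | 0.7-1.6 |
| 20% | 58.5% | 67.5% | 74.8% | 1.5-3.2 |

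The early concentration of linkage matters. A constant hazard reaching 60% at 12 months would give larger figures (1.3 points at 5% mortality, 2.6 at 10%). It would also imply only 1 - 0.4^(1/12) = 7.4% linked at one month, against the 50% that the plan assumes.

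**Non-retention among the linked.** Take a constant hazard with 50% non-retained at 12 months net of death: H = -ln(0.5) = 0.6931 and D = -ln(1 - m). If death is not part of the event, cumulative incidence = H/(H + D) × [1 - 0.5(1 - m)]. At m = 5% this is 0.9311 × 0.525 = 48.9%. If death is part of the event, the composite is 1 - 0.5(1 - m), and Kaplan-Meier estimates it without this bias.

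| Assumed mortality | KM, death censored | Cumulative incidence | Overstatement (points) | Composite, death as event |
|---|---|---|---|---|
| 2% | 50.0% | 49.6% | 0.4 | 51.0% |
| 5% | 50.0% | 48.9% | 1.1 | 52.5% |
| 10% | 50.0% | 47.7% | 2.3 | 55.0% |
| 20% | 50.0% | 45.4% | 4.6 | 60.0% |

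**Arm contrast.** Take one arm at 50% linked by month 1 and 60% by month 12, and the other at 75% and 80%. The Kaplan-Meier difference is 20.0 points. With equal mortality of 5%, 10% or 20% in both arms, the cumulative incidence difference is 20.1, 20.2 or 20.4 points. With unequal mortality, the first table gives an example: at 70% net linkage in both arms, 5% against 10% mortality gives 69.4% against 68.8%, a gap of 0.6 points that Kaplan-Meier would not show.

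**The case against.** The strongest reply is that the article never says deaths are censored in these curves. Its one censoring rule nearby is about loss to follow-up, and event definitions may well stand in the full protocol, which is not shown. That is fair. It makes the overstatement conditional on the usual use of the method. It does not remove the point, because the article names the method for linkage and handles death differently for ART initiation in the same paragraph.

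A reader might go further and infer that both linkage and non-retention are overstated. The documents do not support that for non-retention. A participant who has died is not in care at 12 months, and if death counts as non-retention, Kaplan-Meier is valid for that composite. Naming mortality as a separate outcome hints that death is excluded but does not establish it.

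A reader might also infer that the comparison of arms is materially distorted. With equal mortality it hardly moves. A distortion needs different mortality before linkage, for which the article gives no figure. Accelerated ART follows enrolment in care, so it cannot directly reduce deaths before linkage.

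Finally, the curves are introduced as an addition to the intention-to-treat comparison and mixed models for the secondary outcomes. That stands, and limits the weight of the point.

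**Conclusion.** The point holds for linkage, conditionally and at small size. If deaths are censored, one minus Kaplan-Meier overstates 12-month linkage by about 0.4 to 0.8 points at 5% mortality, 0.7 to 1.6 at 10% and 1.5 to 3.2 at 20%. For non-retention the overstatement (about 1.1 points at 5%, 2.3 at 10%) arises only if death is not counted as non-retention.

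These sizes rest on assumed mortality, a constant death hazard independent of linkage, and the plan's 50% linked by one month. Higher mortality among the unlinked than assumed would enlarge the linkage figures. The primary endpoint, a binary composite analysed by a multilevel model, is not affected. This is a minor improvement to a secondary analysis.

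**What to change.** - **Linkage:** estimate the 12-month proportion by the cumulative incidence function (Aalen-Johansen) with death as a competing event, with cluster-robust or site-bootstrap intervals.
- **Non-retention:** state whether death counts as non-retention. If it does, count it as an event and keep Kaplan-Meier for that composite. If it does not, treat death as a competing event.
- **Mortality:** keep Kaplan-Meier.

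The cost is a few sentences in the plan and a different procedure on the same data. No further data or participants are needed. If the full protocol already settles how death enters these curves, quoting that rule closes the question of definition.
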